## E. Project Procedures

## E1. Clinical Data Collection

For quality assurance data collection, participants will be identified retrospectively and data will be collected electronically using EHR (EMS records, and WFBH medical records) and via telephone follow-up calls.

Paramedics will use a worksheet to obtain the historical and clinical data needed to calculate a HEART score and this will include recording the POC troponin results. This worksheet will be an investigational record integrated into their normal reporting workflow. Data entered on this worksheet will be abstracted retrospectively. Data obtained will include demographic information (age, gender, race, ethnicity), date and time elements, characteristics of chest pain, ECG interpretation, cardiac risk factors (such as, prior coronary artery disease, smoking, hypertension, diabetes, hyperlipidemia, etc), POC troponin value, and the HEART score.

Since all participants will be transported to WFBMC ED, where the HEART Pathway is part of standard care, we will use the electronic medical record (EMR) to obtain ED physician HEART Score assessments and WFBMC troponin results. These data will be compared to paramedic assessments for determination of inter-observer agreement and correlation. We will also use the EMR to track index outcomes and 30 day events that occur within the WFBH system. Data collected from the WFBH EMR will include patient demographics, history and physical examination data, past medical history, cardiovascular risk factors, ECG results, laboratory results, HEART score and HEART Pathway assessments, ED and discharge diagnoses, disposition, index visit length of stay, objective cardiac testing at the index visit or within 30 days, recurrent ED visits, re-admissions, coronary revascularization, and MI or death within the follow-up period.

In addition to electronic surveillance, follow up phone calls will be used to determine outcomes at 30 days. EMS or project staff will contact each participant at 30-90 days following their pre-hospital encounter using a modified version of a previously described scripted follow-up dialogue[^23^](#_ENREF_23) to further clarify events since discharge, identify events occurring at other care facilities, and to determine health care utilization since discharge. Events of interest will include MACE (cardiac death, acute myocardial infarction, and coronary revascularization), hospitalizations, and objective cardiac testing (stress testing and coronary angiography), and recurrent ED visits. Participants still unable to be contacted will be considered censored at their last known contact unless record review reveals an event occurred, in which case the patient will be considered to have experienced an event. Participants unable to be contacted will be searched for in the Social Security Death Master File. In the event of discrepancy between a participant’s event reporting and the medical record, the medical record will be considered correct.

*Rationale for phone follow up:*  In order to determine the accuracy of paramedic HEART Score assessments for MACE we will need to have a low lost-to-follow-up rate. Without telephone follow-up calls patients who seek follow-up or recurrent care or have adverse events at non-WFBH facilities will not be detected. Furthermore, it is common practice for EMS agencies to use phone follow up to contact patients for quality assurance purposes. Using the above methods we expect to have a lost to follow-up rate less than 10%.

E2. Outcomes

*2a. Primary Outcome*

The primary outcome is MACE at 30 days. MACE is a composite outcome of cardiac death, acute myocardial infarction, and coronary revascularization. MACE occurring in patients with a low-risk HEART score assessment will be considered missed MACE. The primary outcome will be used to determine the sensitivity, negative predictive value, specificity, positive predictive value, likelihood ratios, and accuracy for paramedic detection of MACE at 30 days using the HEART score with i-STAT POC troponin testing.

The definition of cardiovascular death will be based on the Action to Control Cardiovascular Risk in Diabetes (ACCORD) trial.[^24^](#_ENREF_24) Death from stroke will not be considered a cardiac death.

Modified ACCORD definition of Cardiovascular Death:

1. Unexpected death: Unexpected death presumed to be due to ischemic cardiovascular

disease, occurring within 24 hours of the onset of symptoms without confirmation of

cardiovascular disease, and without clinical or post mortem evidence of other etiology.

2. Fatal Myocardial infarction (MI): death within 7 days of the onset of documented MI

3. Congestive heart failure (CHF): death due to clinical, radiological or postmortem

evidence of CHF without clinical or postmortem evidence of an acute ischemic event

(cardiogenic shock to be included).

4. Death after invasive cardiovascular interventions: death associated with the intervention,

i.e., within 30 days of cardiovascular surgery, or within 7 days of cardiac catheterization,

arrhythmia ablation, angioplasty, atherectomy, stent deployment, or other invasive

coronary or peripheral vascular intervention.

5. Documented arrhythmia: death due to bradyarrhythmias or tachyarrhythmias not

associated with an acute cardiac ischemic event.

6. Death following non-cardiovascular surgery: death due to cardiovascular causes as

defined above within 30 days of surgery.

The definition of myocardial infarction will be based on the recommendations of the 2012 Joint ESC/ACCF/AHA/WHF Task Force for the Redefinition of Myocardial Infarction:[^25^](#_ENREF_25)

A rise and/or fall of troponin with at least 1 value above the 99th percentile of the upper reference limit with at least one of the following: a) symptoms of ischemia, b) ECG changes indicative of new ischemia, c) Development of pathological Q waves on the ECG, d) Imaging evidence of new loss of viable myocardium or new regional wall motion abnormality. Peri-procedural MI is defined in accordance with the most recent 2012 Universal Definition of MI (Types 4a, 4b, and 5).

Coronary revascularization will be defined as angioplasty with or without stent placement, or coronary artery bypass surgery. Coronary revascularization occurring in patients discharged from the ED without objective cardiac testing will be considered missed coronary revascularization.

*2b. Secondary Outcomes*

Objective cardiac testing will be defined by any stress testing modality, coronary CT angiography, or invasive coronary angiography.

Length of stay (LOS) will be the time from ED arrival to hospital discharge for all patients, whether admitted or not.

Index visit hospitalization will be defined as an inpatient or observation admission (including Observation Unit evaluations ≥6 hours).

Cardiac related non-index hospital admissions and ED visits: Hospital admissions and ED visits occurring during the 30 day follow up period will be categorized as cardiac-related if a cardiac procedure is performed, the primary reason for admission/visit is chest pain, possible ACS, or a discharge diagnosis relates to chest pain, MI, acute coronary syndrome, heart failure, dysrhythmias, pericardial disease, or other cardiac disease. Cardiac procedures include cardiac imaging / stress testing (excluding resting echo), coronary revascularization, and pacemaker or defibrillator insertion.

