While the ED care team will receive report on the POC troponin results (as well as the patient’s clinical features and ECG, as part of a normal EMS verbal report), the ED care team will remain blinded to paramedics’ HEART Scores to allow evaluation of agreement between paramedic and ED provider risk assessments. HEART Score calculation by the ED provider is part of the standard ED care for patients with acute chest pain presenting to the WFBMC ED, which will facilitate assessment for agreement.

To assess the correlation of pre-hospital POC troponin to in hospital POC troponin and central lab troponin, patients in the WFBMC ED will receive a standard ED chest pain evaluation, expected to include an ECG and serial blood draw at ED arrival and 3 hours after arrival for troponin measurement. Blood obtained in the hospital as part of normal care will be used for central lab troponin measurement [AccuTnI+3 assay (Beckman Coulter, California) or TnI-Ultra assay (Siemens, Munich Germany)]. In addition, whenever possible, this blood will also be used to obtain an in-hospital Abbott i-STAT POC troponin measurement. See Table 2 for a summary of troponin measurements.

| Table 2. Troponin measures | | |  |
| --- | --- | --- | --- |
| **Blood Draw #** | **Description** | **i-STAT**  (green-top tube) | **Central lab/Beckmans**  (green-top tube) |
| 1 | Pre-hospital | X^*^ | X^#^ |
| 2 | ED arrival | X^#^ | X^#^ |
| 3 | 3 hours after ED arrival | X^#^ | X^#^ |

For quality assurance, participants will be identified retrospectively and data will be collected electronically using EHR (EMS records, and WFBH medical records) and via telephone follow-up calls. In EMS quality assurance projects, it is customary for EMS agencies to contact their patients by phone to assess their well-being. Therefore, each patient will be contacted 30-90 days following their pre-hospital encounter to determine if they have had MACE (cardiac death, acute myocardial infarction, and coronary revascularization), hospitalizations, and objective cardiac testing (stress testing and coronary angiography). Patients will also have a record review to determine patient demographics and project outcomes including; MACE, hospitalization, hospital length of stay, and objective cardiac testing.

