**F. Statistical Plan**

F1. Overview

The primary concept of the PARA-HEART project is to evaluate whether paramedics can be taught to calculate a HEART score accurately with acceptable intra-observer reliability (when compared to ED physician assessments). This project is a clinical pilot study in order to generate data to support a larger and non-observational implementation. If we are able to show that these scores can be reliably predict MACE and agree with ED physicians assessments, then we can start using the HEART score in the pre-hospital setting to alter care and transport triage and destination plans.

F2. Sample Size and Power

The PARA-HEART project is a clinical pilot study in which we hope to demonstrate that paramedics are able to achieve 98% sensitivity for the detection of MACE. To achieve a sensitivity of 98% with a lower bound of the 95% confidence interval that exceeds 90% we will need at least 50 patients with MACE events. Assuming a 10% MACE rate among our chest pain population,[^4-7^](#_ENREF_4) to include 50 patients with adverse events we will need a total sample size of 500 patients.

F3. Analysis Plan and Statistical Methods

The percentage of patients identified by paramedics using the HEART Score with POC troponin testing as high- and low-risk, the sensitivity, specificity, and positive and negative predictive values, positive and negative likelihood ratios, and accuracy for MACE will be calculated. Corresponding 95% exact binomial confidence intervals will be computed.

The proportion of patients receiving objective cardiac stress testing, cardiac catheterization, myocardial infarction, or cardiac death during the index hospitalization will be estimated for subjects classified as high and low risk by ED physicians and compared with those classified as high and low risk by paramedic assessment. Cardiac-related ED visits and readmission to the hospital will be calculated at 30 day follow-up. LOS will be reported using descriptive statistics, including median and inter-quartile range as this outcome tends to have a nonparametric distribution.

HEART scores calculated by the blinded primary ED provider will be compared to the HEART scores obtained by the paramedics. Raw percent agreement and kappa scores will be determined to assess intra-observer reliability. A kappa of >0.75 will be defined as excellent agreement, 0.60-0.74 will be defined as acceptable agreement, and <0.59 will be defined as unacceptable agreement.

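### The 30-90 day outcome call may be made by EMS staff, with no rule excluding the scoring crew or masking the caller to the paramedic HEART score and troponin

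*Protocol*

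**What the plan says.** **Who calls.** Protocol E1: "EMS or project staff will contact each participant at 30-90 days following their pre-hospital encounter", "using a modified version of a previously described scripted follow-up dialogue". No further condition is placed on the caller.

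**What the call is for.** E1 uses it to establish 30-day outcomes, and the primary outcome in E2 is MACE at 30 days. E1 describes the record review as limited in reach: "We will also use the EMR to track index outcomes and 30 day events that occur within the WFBH system". Its rationale for the calls is that "Without telephone follow-up calls patients who seek follow-up or recurrent care or have adverse events at non-WFBH facilities will not be detected".

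**Who produces the result under test.** E1: "Paramedics will use a worksheet to obtain the historical and clinical data needed to calculate a HEART score"; the troponin value is recorded there too. "This worksheet will be an investigational record integrated into their normal reporting workflow". D4 adds that the worksheet stays out of the permanent medical record. F1 gives the project's purpose as to "evaluate whether paramedics can be taught to calculate a HEART score accurately".

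**What is blinded.** D4: "the ED care team will remain blinded to paramedics’ HEART Scores to allow evaluation of agreement". Nothing comparable is stated for the follow-up caller.

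**Other safeguards.** E1 lets the medical record prevail over the participant's account and sends participants who cannot be reached to a death-file search. E4 has two reviewers adjudicate MACE from index records and follow-up records, with claims data if available. F4 counts missing outcomes as no event and plans a sensitivity analysis of that assumption.

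**The concern.** In a diagnostic accuracy study, whoever collects the reference outcome should not know the index test result. The protocol applies this principle to the agreement analysis, by keeping the paramedic score from the ED team, but not to the accuracy analysis, which is its first primary hypothesis.

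The wording permits a caller from the agencies whose scoring is being assessed, and permits any caller to know the risk class. A caller who knows that a patient was scored low-risk may probe less or accept a brief reassurance. An outside event lost in this way is a false negative that becomes a true negative, and both sensitivity and NPV rise. The reverse error, recording an event that did not occur, is less likely to survive adjudication. F1 intends a favourable result to support changes to care and transport plans, so an upward bias matters.

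**Working it through.** **1. The plan's own figures.** F2 assumes a 10% MACE rate and wants 50 events: 50 / 0.10 = 500 patients, which reproduces. F2's aim is 98% sensitivity with a lower 95% bound above 90%. F3 specifies exact binomial intervals. For 49 of 50, the exact (Clopper-Pearson) lower bound is the 2.5% quantile of a Beta(49, 2) distribution, which is 0.8935, or 89.4%. So 50 events with one miss fall just short of F2's own bound. That is a separate matter of sample size, but it fixes the baseline here.

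**2. One missed event, not elicited.** E2 defines missed MACE as MACE in a patient scored low-risk. If the event is not elicited, it leaves the denominator of sensitivity.

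| Truth | Recorded | Sensitivity | Exact 95% lower bound | Above 90%? |
|---|---|---|---|---|
| 49 detected, 1 missed | all 50 | 49/50 = 98.0% | 89.4% | no |
| 49 detected, 1 missed | 49; the miss not elicited | 49/49 = 100% | 0.025^(1/49) = 92.7% | yes |

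One event moves the result across F2's bound.

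**3. Two missed events, one not elicited.** 48/50 = 96.0% (lower bound 86.3%) becomes 48/49 = 97.96% (lower bound 89.1%). Both estimates are below 98% and both lower bounds are below 90%. The estimate moves by about 2 percentage points, but neither criterion is crossed.

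**4. NPV.** The protocol gives no low-risk share. Assume 20% to 40% of 500, that is 100 to 200 patients. An unelicited event stays in the NPV denominator and moves to the numerator, so each one adds 1/100 = 1.0 to 1/200 = 0.5 percentage points. At 100 low-risk patients with three misses, 97/100 = 97.0% becomes 98/100 = 98.0%. At 200 with five misses, 195/200 = 97.5% becomes 196/200 = 98.0%.

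**5. Which events are exposed.** Index and 30-day events inside WFBH come from the EMR whoever calls. The exposed set is MACE that is post-index, outside WFBH, in a low-risk patient, and not elicited on a call by someone aware of the score. The documents give no rate for any of these conditions, so the figures above are consequences of one event, not a forecast.

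**6. Whether other safeguards catch such an event.** Adjudicators can rule only on what the records and follow-up contain. Claims data are conditional. The death-file search covers participants without follow-up and finds only deaths. The F4 sensitivity analysis concerns missing outcomes, not a completed call recorded as event-free.

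**The case against.** The strongest reply is that the protocol describes a controlled process. The call is scripted, and it asks about hospitalizations, cardiac testing and repeat ED visits as well as MACE, so an outside event has several chances to surface. The components of MACE are hard events. Every participant is taken to the WFBMC ED for an evaluation expected to include serial troponins, so many events will be found at the index visit. Claims data may reveal others. Project staff belong to the team promoting the tool and are not disinterested either. Caller assignment may also be settled in the manual of procedures described in G3.

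Much of this stands. It narrows the exposure and makes the direction of bias plausible rather than shown. It also means that masking matters more than who employs the caller. It does not close the gap: a script fixes the questions, not the persistence, and E1 itself names EMS staff as callers without a condition.

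Four stronger readings are tempting and are not supported:

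- A reader might infer that EMS agencies keep the worksheet and that the scoring paramedic will call. The documents say neither; they only leave both possible.
- A reader might infer that the call is the sole route to outside events. E4's claims data, where available, and the death file are partial alternatives.
- A reader might take 96.0% becoming 97.96% as a changed verdict. It reaches 98% only by rounding, and both lower bounds miss 90%.
- A reader might conclude that EMS must make no calls, or that callers must also be masked to the ED physician's score. Protecting the accuracy of the paramedic score requires neither.

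**Conclusion.** The point holds as an avoidable weakness in how the primary outcome is ascertained, not as evidence of bias. E1 leaves the caller unmasked to the index test and does not exclude the scoring crew, while the call is the stated route to MACE outside WFBH. If bias occurs, it most plausibly raises sensitivity and NPV.

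One unelicited missed event is enough to turn a lower bound of 89.4% into 92.7%, from failing to meeting F2's aim. This rests on F2's 50 events, one true miss, and that miss being a post-index event outside WFBH. How likely this is cannot be estimated from the protocol. The correction is worth making because it is cheap and because the target leaves room for so few missed events.

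**What to change.** Add to E1 that the follow-up call is made by a person who neither treated nor scored the patient and who has no access to the paramedic worksheet, the prehospital POC troponin result or the paramedic HEART score, preferably the project staff whom E1 already names. Record the caller's role for every call. If EMS staff do call, report outcomes by type of caller. The caller may still be given the event information needed to clarify events already in the WFBH record.

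**Cost.** A short addition to E1 and a matching entry in the manual of procedures. Some calls move to project staff: at most 500 over the 12-month pilot and 3-month close-out in section I, about 500/65 = 7.7 a week. The real burden is that calling must be kept separate from worksheet abstraction, which may need some division of duties. No extra visits and no change to patient care follow.

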### E3. Detection

MACE will be assessed at 30 days through the EMR and scripted phone follow up calls. Participants without EMR or phone follow up data will be searched for in the Social Security Death Master File.

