## E4. Endpoint Adjudication

A consensus of two reviewers ([name], [name]) will adjudicate elements required to measure the occurrence of all MACE endpoints. Reviewers will adjudicate return visits to the ED or readmissions within the ED are cardiac related if this unclear based on preliminary review by project staff. To make these assessments, reviewers will be provided the participant’s index and discharge records, records obtained from follow-up including claims data when available, and project definitions. Records will have patient identifiers removed. Reviewers will complete a reviewer outcome form recording the occurrence of safety endpoints, which will be stored in our secured electronic database. Any disagreements will be settled by consensus between the two reviewers, or the involvement of a third reviewer ([name]).

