## F4. Missing Outcome Data

Based on prior studies we expect >90% to have complete follow-up data from the EMR or phone follow up calls. Participants without follow up data will be searched for the Social Security Death Master File. Those with missing outcome data will be treated as censored and will be considered to have not had a safety event. A planed sensitivity analysis will be used to test this assumption.

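### The cardiac-death definitions have no category for death of undetermined cause, so a later death known only from the Death Master File in a discharged low-risk patient would probably be scored as no MACE

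*Protocol*

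**What the plan says.** Section E2 (2a, Primary Outcome) defines the endpoint: "MACE is a composite outcome of cardiac death, acute myocardial infarction, and coronary revascularization". Cardiac death is then set by a modified ACCORD list of six categories. The first begins "Unexpected death: Unexpected death presumed to be due to ischemic cardiovascular" disease, and requires death within 24 hours of symptom onset with no evidence of another cause. The other five cover fatal MI, heart failure, death after an invasive cardiovascular intervention, documented arrhythmia, and cardiovascular death after non-cardiovascular surgery. Death of undetermined cause is not on the list.

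Three sections send patients to the Death Master File. E1 says: "Participants unable to be contacted will be searched for in the Social Security Death Master File". E3 says: "Participants without EMR or phone follow up data will be searched for in the Social Security Death Master File". F4 repeats the search for those without follow-up data.

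Three further rules bear on what happens next:
- E1, censoring: "Participants still unable to be contacted will be considered censored at their last known contact unless record review reveals an event occurred".
- F4, default: "Those with missing outcome data will be treated as censored and will be considered to have not had a safety event", followed by "A planed sensitivity analysis will be used to test this assumption".
- E4, adjudication: "reviewers will be provided the participant’s index and discharge records, records obtained from follow-up including claims data when available, and project definitions".

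No section says how a death found in the file, with no cause attached, enters a composite limited to cardiac death.

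**The concern.** The search exists to catch deaths that the record review and the telephone call both miss. For it to affect the primary outcome, a death it finds has to be classifiable as cardiac or not. For at least one kind of patient the list gives adjudicators nothing to classify with, and the likely result is no event.

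That patient sits where the design is most sensitive. A low-risk patient (HEART score 3 or less) who is sent home and dies within 30 days would, if counted, be a missed MACE, the false-negative cell that enters both co-targets of 98% sensitivity and 98% NPV. Leaving such a death out moves both estimates in favour of the tool under test.

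**Working it through.** **Step 1. Check a bare date of death against each definition.** Assumption: the file supplies the fact and date of death only. The protocol does not describe its contents. Every participant is taken to WFBMC ED, so an index record exists and adjudicators receive it (E4).

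| E2 definition | What it needs | Can index record plus date of death meet it? |
|---|---|---|
| 1 Unexpected death | Presumed ischemic cause; within 24 hours of symptom onset; no evidence of another cause | Possibly, if death falls within 24 hours of the index symptoms |
| 2 Fatal MI | Within 7 days of a documented MI | Yes, but that patient already has MACE through the MI |
| 3 Heart failure | Clinical, radiological or postmortem evidence that CHF caused death | Not from a date alone |
| 4 Invasive intervention | Within 30 days of cardiovascular surgery or 7 days of catheterization and similar | Yes; after a diagnostic catheterization without MI or revascularization it adds a new MACE |
| 5 Arrhythmia | Documented arrhythmia as cause | Not from a date alone |
| 6 Non-cardiovascular surgery | Cardiovascular cause, within 30 days of surgery | Not from a date alone |

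**Step 2. Isolate the patient left over.** Low-risk, discharged with no MI, procedure or surgery, no later records, dead more than 24 hours after symptom onset but within 30 days. Definitions 2, 4 and 6 fail because there was no MI, intervention or surgery. Definition 1 fails on timing, and no later symptom onset is recorded. Definitions 3 and 5 fail for lack of evidence. None of the six is met.

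**Step 3. Follow both ways the plan could handle this death.**
- As a missing outcome: F4 scores no event, taking its safety event to mean MACE. The planned sensitivity analysis then covers the death, though its method is not given.
- As a known death: it goes to adjudication, fits no category and is not cardiac death. The F4 sensitivity analysis tests the missing-data assumption, so it may not reach this death.

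E1 lifts censoring only when record review shows an event, and does not say whether a match in the file counts as record review.

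**Step 4. Size for sensitivity.** Inputs from F2 and F3: 50 MACE, 98% sensitivity, exact binomial 95% intervals. The plan's total reproduces: 50 / 0.10 = 500. A sensitivity of 98% on 50 events means 49 detected and 1 missed. Each added low-risk death raises the denominator by one and leaves the numerator unchanged:

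| Low-risk deaths added | Starting from 49/50 | Starting from 50/50 |
|---|---|---|
| 0 | 49/50 = 98.0% (89.4 to 99.9) | 50/50 = 100% (lower bound 92.9) |
| 1 | 49/51 = 96.1% (86.5 to 99.5) | 50/51 = 98.0% (lower bound 89.6) |
| 2 | 49/52 = 94.2% (84.1 to 98.8) | – |

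From a perfect result, one such death takes the lower bound from above the 90% criterion in F2 to below it.

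**Step 5. Size for NPV.** The documents give no low-risk share, so I assume 100 to 200 low-risk patients and keep the same single miss. Counting one death moves it from true negative to false negative, with the denominator unchanged: 99/100 = 99.0% becomes 98/100 = 98.0%; 199/200 = 99.5% becomes 198/200 = 99.0%. The shift is 0.5 to 1.0 percentage points, and in this example NPV does not fall below 98%. The case rests on sensitivity.

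**Step 6. Direction in high-risk patients.** An uncounted cardiac death there removes a true positive: 49/50 = 98.0% against 50/51 = 98.0%. The effect on sensitivity is negligible, so it does not offset the low-risk effect.

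**The case against.** A reader might infer something stronger: that a death found only in the file can never meet any definition, is always scored as no MACE, and so can never add an event. The documents do not support that. Index records exist for everyone and reach the adjudicators, with claims data when available. Definition 4, an interval rule, can add a new event from a date of death alone. Definition 2 can be met too, and definition 1 possibly. Nor does any sentence say that a found death is scored as no event. The F4 default concerns missing outcomes, and a known death is arguably not one.

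Three further objections deserve weight. The contents of the file are an assumption. The documents give no rate for such deaths: E1 expects loss to follow-up below 10%, fewer than 50 of 500, and being searched for is not the same as being found dead. And rules of this kind could go in the manual of procedures, which is to hold measurement definitions (G3), or be left to the adjudication committee (G5).

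The first two stand as limits on size and certainty. The third stands only in part. The protocol fixes the endpoint in E2 with a specific list, and adjudicators are told to apply the project definitions. A committee following that list has no category for this death, so leaving the matter to judgement does not remove the lean towards no event.

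**Conclusion.** The gap is real but narrow. E2 gives no category for death of undetermined cause, while E1, E3 and F4 set up a search that may find exactly such deaths. For a low-risk patient discharged without MI, procedure or surgery who dies after the first 24 hours, the probable result is no MACE under either reading of the plan. That is an inference from the rules, not a rule the protocol states.

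The number affected is unknown and likely very small, but at 50 events one death is worth about two percentage points of sensitivity (98.0% to 96.1%). The conclusion rests on the file giving only fact and date of death, on the planned 50 events, and on the death occurring in a low-risk patient. It warrants a change before outcomes are known, because the omission favours the tool and the correction is cheap.

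**What to change.** Add one line to the modified ACCORD list in E2: a death within 30 days of the pre-hospital encounter whose cause cannot be established from the index, follow-up or claims records, including one found only in the Death Master File, counts as cardiac death for the primary outcome. This makes such a death a known outcome, so the F4 default no longer applies to it.

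Report sensitivity and NPV with these deaths excluded as a sensitivity analysis, so that readers can see what the convention contributes.

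The cost is one definition line and one table row, with no new data or staff. The downside is that a few non-cardiac deaths may be counted as MACE, making sensitivity and NPV slightly less favourable where they fall in low-risk patients.
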